#### Randomization and masking

After the completion of the baseline assessment, eligible participants will be randomly allocated to two study groups. The random allocation will be conducted by an independent researcher with an external randomization service (i.e., sealedenvelope.com), using random permuted block sizes (i.e., 4 or 6) to ensure balanced group numbers. Participants will not be blinded due to the nature of the intervention. Participants will be reminded to keep the intervention content confidential and not discuss this with participants in the control group to avoid contamination. Assessor-blind is not adopted as measurements are self-reported. Assistance provided by caregivers and research assistants might be needed for those who have difficulties in filling out surveys.

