Currently, there is no effective treatment to cure SCI, although the life expectancy of SCI survivors is now equivalent to the general population given the improvement in medical treatment. Patients often suffer immediate and

irrecoverable neurological loss and severe disabilities that last for the rest of their lives. Prior research has indicated that people with paraplegia/tetraplegia following traumatic SCI have a lower quality of life than the general Hong Kong population and they need more medical care, psychosocial support, and environment adaptation [4]. People with SCI experience various secondary physical and psychological consequences during the long recovery process. Physical inactivity, depression, and chronic pain are the major challenging problems and have detrimental effects on these people's quality of life and well-being. Approximately 50% of the SCI population have no engagement in leisure-time physical activities such as wheeling, therapeutic exercise, or equipment-assisted walking after they are discharged from inpatient rehabilitation, and this inactivity is linked with increased risk for depression, pain, and poor quality of life [5]. Physical inactivity is not only determined by people's levels of injury and severity at post-SCI but also related to their behavioural patterns and psychological conditions [6]. Those with more negative emotions and low levels of self-efficacy will have lower motivations and engagement in physical activities. Depression (caused by a variety of medical, psychological, and social factors) is the most common mood problem in people with SCI, and it interferes with the ability of individuals to engage in daily life activities and affects their life satisfaction [7]. The prevalence rate of depression at post-SCI ranges from 9.8% to 63.9% at post-SCI, which is significantly higher than those of non-SCI counterparts (5.3%-11.3%) [8]. Chronic pain (persisting for more than 12 weeks) also remains a significant problem at post-SCI, with an estimated prevalence rate of around 70%-80% during long-term rehabilitation [9]. Chronic pain has a significant negative impact on the physical and emotional functioning of people with SCI, and a strong interrelationship has been found between pain and depression among people with SCI [10].

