People with SCI will be included if they are: (1) at least 18 years old; (2) currently living in the community and having SCI for more than 6 months; (3) complete injury at the C6 or below or incomplete injury at any level; (4) having a computer/smartphone with audio-speaking function and Zoom software, and internet access in a secure place; (5) using a wheelchair for at least 2 hours a day and having approval from their physicians to perform exercises; (6) having no problems in hearing, verbal communication and vision; and (7) able to communicate in Cantonese and to provide informed consent.

People with SCI will be excluded if they are: (1) presenting with any significant cognitive impairment or brain injury; (2) engaged in ongoing psychotherapy or

any other physiotherapy/exercise/relaxation interventions; (3) physically active for more than 150 minutes per week; and (4) experiencing significant psychotic symptoms, substance misuse or medically unfit for the exercise and psychological programme as diagnosed by their physicians.

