#### Sample size

As this proposed study is to develop and evaluate the feasibility, acceptability, and preliminary effectiveness of the PPI intervention, a widely acceptable sample size (i.e., 30 participants in each study group) for a preliminary analysis to examine intervention feasibility and to estimate a between-group effect will be adopted [22]. Considering a 20% attrition rate, 36 people with SCI per study group (i.e., 72 people in total) will be recruited. A purposive sampling by key informants (containing both participants who completed the whole intervention sessions and those who withdrew from the intervention period) will be conducted for focus-group interviews (i.e., 4-5 participants per group), until saturation of the information was reached.

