## Data analysis

All quantitative data from the pre- and post-tests will be numerically coded, summarized (with descriptive statistics), and analyzed using IBM SPSS 26. Both intention-to-treat and per-protocol analyses will be performed. Effect sizes of between-group comparisons will be estimated using Cohen's *d* which is applicable for small sample sizes [29]. Comparison of baseline information between two study groups will be performed by t-test, Mann-Whitney U, and/or Chi-square tests depending on the nature of the data. The generalized estimating equation will be used to assess the changes in the outcome measurements between groups over time, followed by contrast tests. Co-variance (if any found in the baseline comparison) will be adjusted during the analysis of intervention effects. Subgroup analysis will be conducted for certain factors (e.g., complete and incomplete injury or intervention completion and non-completion). Level of significance is set at  $p < 0.05$  (2-tailed).

Focus group interview data will be content analyzed. Tape-recorded interviews will be transcribed into Cantonese by one research assistant and cross-checked by the other research assistant. Codes will be discussed and agreed between our team members, combined to form categories/subcategories, and explained with verbatim data. Any discrepancy in coding/category will be discussed and final themes/subthemes will be confirmed by our team.

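### Blocks that balance only group numbers leave injury completeness to chance, although the protocol links injury severity to inactivity and plans a complete versus incomplete analysis: a cheap improvement, not an error

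*Protocol*

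**What the plan says.** The Randomization and masking section describes allocation after baseline by an external service, "using random permuted block sizes (i.e., 4 or 6) to ensure balanced group numbers". It names no stratification factor and no minimisation. The Sample size section states that "36 people with SCI per study group (i.e., 72 people in total) will be recruited".

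Three other places bear on the choice:

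- The Introduction says: "Physical inactivity is not only determined by people's levels of injury and severity at post-SCI but also related to their behavioural patterns". Leisure-time physical activity is the first primary outcome listed.
- Inclusion criterion 3 admits "complete injury at the C6 or below or incomplete injury at any level", so both injury types will be in the trial.
- The Data analysis section says: "Subgroup analysis will be conducted for certain factors (e.g., complete and incomplete injury", with intervention completion as the other example.

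The Data analysis section also plans to adjust the effect estimates for covariates that show up in the baseline comparison, which uses t, Mann-Whitney and chi-square tests. The only significance level given is two-sided 0.05. Under Preliminary effectiveness, effect sizes such as Cohen's d are to be used to size a later full trial.

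**The concern.** The protocol links injury severity to one of its primary outcomes and gives completeness as an example of a subgroup factor, but its allocation method leaves the balance of that factor to chance. At 36 per arm a sizeable gap is not rare. If completeness predicts activity, such a gap moves a simple between-group difference in this one trial, and the Cohen's d from this trial feeds the sample size of the next one. A gap also makes the arm comparison within each injury type less even. The planned remedy, adjustment after a baseline test, responds to whether a gap is statistically significant and not to whether the covariate is prognostic.

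The protocol itself fixes the randomisation method, so this is not a detail left to an analysis plan that is not at hand.

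**Working it through.** **Inputs.** From the protocol: 36 per arm, 1:1, blocks of 4 or 6, two-sided 0.05. Assumed: the share *p* of participants with complete injury, varied from 20% to 60% because the protocol gives no figure. The 15-point threshold is a convention chosen for illustration.

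**The protocol's own figure.** 30 × 1.20 = 36 per arm, 72 in total, as stated. (Dividing by 0.80 instead gives 37.5, so 38; that is a separate matter and hardly affects this point.)

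**Step 1: chance of a gap of 15 points or more.** Five participants are 5/36 = 13.9 points and six are 6/36 = 16.7, so the event is a difference of at least six. With X₁ and X₂ independent Binomial(36, *p*), sum P(X₁ = i)·P(X₂ = j) over |i − j| ≥ 6. As a check, unstratified blocks of 4 or 6 were simulated (20,000 trials per share).

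**Step 2: would the baseline comparison pick it up?** The standard error of the gap is √(2p(1 − p)/36). At *p* = 50% it is √(0.5/36) = 0.118, so a 15-point gap gives z = 0.15/0.118 = 1.27 and p = 0.20. Reaching p < 0.05 needs about 1.96 × 0.118 = 0.23, or 23 points. The last column repeats the sum in step 1, keeping only pairs whose uncorrected chi-square test has p ≥ 0.05, divided by the step 1 total.

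| Share complete (assumed) | P(gap ≥ 15), exact | Same, simulated blocks | p-value of a 15-point gap | Gap needed for p < 0.05 | Gaps ≥ 15 that stay at p ≥ 0.05 |
|---|---|---|---|---|---|
| 20% | 10.4% | 10.9% | 0.11 | 18.5 points | 54% |
| 30% | 15.6% | 15.7% | 0.16 | 21.2 points | 66% |
| 40% | 18.5% | 18.7% | 0.19 | 22.6 points | 73% |
| 50% | 19.5% | 19.3% | 0.20 | 23.1 points | 77% |
| 60% | 18.5% | 18.4% | 0.19 | 22.6 points | 73% |

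The maximum is at 50%. At 10% complete the probability is only 3.1%.

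**Step 3: the same blocks within two strata.** In 8,000 simulated trials per share, no gap of 15 points or more occurred at any share from 20% to 60%. The mean absolute gap fell from about 7 to 9 points to about 1.5, and the largest seen was about 8.

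**Step 4: what a gap could do to an estimate.** Shift = gap × prognostic difference. A 22-point gap is about the 95th percentile at 30% to 50% complete. With an assumed prognostic difference of 0.5 to 0.8 SD, the unadjusted effect shifts by 0.22 × 0.5 = 0.11 to 0.22 × 0.8 = 0.18 SD. The standard error of d is about √(2/36) = 0.24. At the mean gap the shift is 0.07 × 0.5 = 0.04 to 0.09 × 0.8 = 0.07 SD.

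**The case against.** The strongest reply is that nothing here is wrong. Permuted blocks are used to equalise arm sizes and they do so. Unstratified allocation is valid, and chance imbalance is already reflected in the confidence intervals. In a 72-person pilot aimed at feasibility and preliminary effects, stratification is a preference. This stands, and it sets the weight of the point.

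Other parts also stand:

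- **The size of the harm is modest.** The documents give no prognostic difference, so the 0.11 to 0.18 SD shift is an illustration of an extreme case and smaller than the standard error of 0.24.
- **The GEE partly protects itself.** It compares change between groups over time, and a stable difference in activity between injury types largely cancels. The shift applies to unadjusted between-group comparisons, which may include Cohen's d.
- **Uneven subgroups cost little.** With 28 complete injuries, a split of 18:10 instead of 14:14 (8/36 = 22 points) raises the standard error by √[(1/18 + 1/10)/(2/14)] = 1.04, about 4%. The subgroups are thin because the trial is small, and stratifying does not change that.
- **The Introduction does not call completeness a strong predictor.** It mentions level and severity on the way to behavioural and psychological factors. Injury level would stay unstratified under the fix.

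A reader might infer that completeness is already known for everyone at randomisation because inclusion criterion 3 mentions it. The text does not support this. A person injured at C6 or below qualifies either way, so the criterion settles completeness only above C6. The listed baseline items include level of injury but not completeness.

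The reply that the Data analysis section already handles imbalance stands only in part. If a 0.05 threshold is used, it misses 54% to 77% of gaps of 15 points or more, depending on the assumed share. It would catch most of the largest ones.

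**Conclusion.** The point holds as a cheap improvement. The allocation balances only numbers, and a gap of 15 points or more on completeness would arise in about 10% of trials at 20% complete, about 16% at 30%, and 18.5% to 19.5% at 40% to 60%. Stratified blocks reduce that to none in simulation. The planned baseline-test rule, if applied at 0.05, would usually leave a 15-point gap unadjusted; at a 20% share it would miss only slightly more than half of the gaps that large.

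Two stronger readings are tempting. One is that about one trial in five would start out of balance; that is a ceiling, and it depends on a share of complete injuries that the protocol does not state. The other is that the effect estimate is biased; over repeated randomisations it is not. What is at issue is balance and precision in one small trial whose effect sizes carry forward to the next.

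**What to change.** **Randomization and masking.** Record completeness of injury at screening for every participant, whatever the level. Stratify the permuted blocks of 4 or 6 by complete versus incomplete injury.

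**Data analysis.** Prespecify that stratum in the between-group estimates, including the Cohen's d used to size the future trial, in place of selecting covariates by baseline tests. In the GEE, add a stratum-by-time term as well as the main effect. With complete data, a main-effect term alone left the group-by-time contrast and its standard error unchanged.

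**Cost.** One field in the external randomisation service and a few model terms. Completeness must be established before allocation, which the eligibility criteria do not already guarantee. Two strata mean one more possibly unfinished block, so arm sizes may differ by one or two more. The limit is 6 in all: each stratum can end on a block of 6 cut after three allocations to the same arm, and 3 + 3 = 6. Such a difference would be rare. With a single two-level factor, over-stratification is not a concern at 72 participants.

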### The control group

Participants in the control group will receive a video call (approximately 60 minutes each week for eight weeks) from the trained research assistant with psychological background, i.e., to provide general physical and psychological suggestions (e.g., encouragement of performing physical activities, and communication skills with family members/friends, and engagement in the community life). This is to control the contact effects of the PPI intervention.

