### Ethical considerations

Ethical approval will be obtained from the Hong Kong Polytechnic University. This study will be performed in accordance with the Helsinki Declaration. Written informed consent will be obtained from all participants before the baseline assessments of the study, and will also be obtained from purposely sampled participants prior to all focus-group interviews. Participation is entirely voluntary for people with SCI and they can withdraw from the research at any time without any penalty. Participants' identities and data (information

collected and videotape records) will be protected by maintaining anonymity and confidentiality. Only authorized personnel can access the data for analysis.

(iv) Data processing and analysis

Feasibility and acceptability

**The feasibility** assessment of subject recruitment and follow-up will include (1) time taken to recruit the target sample size; (2) recruitment rate: the number of eligible participants approached who agree to consent divided by all subjects eligible to participate; (3) retention rate: the number of participants who complete the study divided by all participants who agree to consent; (4) drop-out rate: the number of participants who dropped out after randomization divided by all participants who agree to consent; and (5) reasons for dropping out will be collected from participants who dropped out.

**The acceptability** of the intervention will be indicated by (1) adherence rate: the number of PPI intervention sessions practiced divided by the total number of required sessions; (2) adverse events record associated with PPI intervention; and (3) satisfaction: participants' satisfaction with the intervention will be assessed with the Client Satisfaction Questionnaire [25]. The acceptability of the intervention will also be assessed by focus-group interviews with a purposive sample of participants who completed the whole intervention sessions and those who withdrew from the intervention period. Participants' perspectives about the acceptability, strengths, and limitations of the study and suggestions on the improvements of the interventions will be explored.

Preliminary effectiveness

All participants will be assessed at pre-, post-intervention, and 3-month follow-up by the research assistant. A self-designed form will be used to collect data on participants' socio-demographics and medical history, including age, gender,

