#### Data collection and processing

With participants' written consent, pre-intervention test will be conducted face-to-face (or online if participants cannot come to the study site) by filling out the questionnaires by the participants by participants on their own. Assistance for those who have difficulties in filling out surveys will be provided by their caregivers or research assistants. At post-intervention and 3-month follow-up, the research assistant will use the same set of outcome questionnaires but the evaluation will be online. Focus groups will be conducted online as described above in the 'feasibility and acceptability' section. With their consent, the interviews (and intervention sessions) will be audio-taped for content analysis.

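### Assessor blinding is waived because outcomes are self-reported, yet research assistants collect and may help complete the questionnaires, and the same role treats the control arm only

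*Protocol*

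**What the plan says.** The Protocol, under Randomization and masking, states "Participants will not be blinded due to the nature of the intervention" and then "Assessor-blind is not adopted as measurements are self-reported". The sentence that follows reads "Assistance provided by caregivers and research assistants might be needed for those who have difficulties in filling out surveys".

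Other sections say who handles the outcome data:

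- Preliminary effectiveness: "All participants will be assessed at pre-, post-intervention, and 3-month follow-up by the research assistant".
- Data collection and processing, on the two visits after randomization: "At post-intervention and 3-month follow-up, the research assistant will use the same set of outcome questionnaires but the evaluation will be online". The same paragraph repeats the provision for help: "Assistance for those who have difficulties in filling out surveys will be provided by their caregivers or research assistants".
- The control group: the weekly video call of about an hour, for eight weeks, comes "from the trained research assistant with psychological background".
- Interventions: the PPI sessions are led by an experienced social worker.
- Data analysis: focus-group recordings are transcribed "by one research assistant and cross-checked by the other research assistant", so there are at least two people in this role.

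**The concern.** The reason given for not blinding assessors is that nobody but the participant produces the score. The Protocol's own account of data collection does not bear that out: a member of staff runs each assessment and may help to complete the form. That member of staff holds the same job title as the person who treats the control arm, and the PPI arm has no such overlap.

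A participant who reports mood or pain to the person who has counselled them for eight weeks may answer differently from one who reports to someone else. A helper who knows the allocation may also affect how items are read or recorded. If that happens more in one arm, it enters the between-group difference. The outcomes exposed are the PHQ-9 and the pain rating, two of the three primary outcomes. The trial is a pilot, but it plans two-sided tests at 0.05 and intends to use its effect sizes to size a later full trial, so a distorted difference would carry forward.

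**Working it through.** The Protocol gives no figure for this point, so there is nothing to recompute. The check sets the sections side by side.

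**1. Is there an assessor?** Yes. Preliminary effectiveness and Data collection and processing both assign the assessments to the research assistant.

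**2. Can that person affect the answers?** Sometimes. At baseline participants complete the forms themselves. The follow-up visits use the same questionnaires online, but self-completion is not restated there. Help is reserved for participants with difficulty and may come from a caregiver or a research assistant. No expected rate is given.

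**3. Does the role overlap with treatment, and equally in both arms?**

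| Arm | Treated by | Follow-up collected, and possibly helped, by | Overlap of role |
|---|---|---|---|
| Control | Research assistant | Research assistant | Yes |
| PPI | Social worker | Research assistant | No |

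**4. Does any section separate the duties?** No. At least two research assistants exist, but their tasks are divided only for transcription and cross-checking. Nothing keeps the control-call provider away from that participant's follow-up forms, and nothing keeps the collector or helper unaware of allocation. Study attrition and data fidelity also has the research assistant prompting attendance at the online meetings, which is a further route to learning the allocation.

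**5. Which visits are affected?** Randomization follows the baseline assessment, so only the post-intervention and 3-month visits are exposed.

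**6. Which primary outcomes are affected?** The PHQ-9 and the pain rating. Physical activity is recorded by a Fitbit. It is therefore not self-reported, and the stated reason does not describe it, but a device reading depends less on an assessor and this adds nothing to the harm.

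**7. What could separating the duties remove?** Only the added influence of the collector or helper. The participant still supplies the score and knows the allocation.

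**The case against.** The best defence is that the text shows a shared job title and no more. The control caller is described by a particular background, other sections speak of research assistants in the plural, and at least two exist. One may make the calls and another collect the data. That is correct, and a reader might infer from the wording that control participants will be assessed by their own provider. The documents do not support that; they only fail to exclude it.

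Second, help is conditional and may come from caregivers. A reader might infer from the eligibility criteria (complete injury at C6 or below, wheelchair use) that help will be common. The criteria also admit incomplete injury at any level and require a computer or smartphone, and no rate is stated, so this remains conjecture.

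Third, a reader might try to size the bias by multiplying a share of participants helped by a shift in score. Neither quantity is in the Protocol, so any such product would reflect only what was assumed. The direction is open too: control participants answering to please their provider would shrink the difference, while a helper who expects the new intervention to work could widen it.

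Fourth, this might be read as the one avoidable bias left once participants are unblinded. The Protocol does not support a ranking of that kind, and masking the collector would leave participants' own reporting bias in place.

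Last, this is a declared open-label pilot, which lowers the stakes, and full masking may not be achievable with existing staff. Both points stand. What survives is narrower: the reason given for the waiver does not match the described procedure, and the possible overlap falls on one arm.

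**Conclusion.** The point holds in limited form. The waiver rests on a reason that the Protocol's own data-collection sections undercut, and the Protocol leaves open that control participants, but not PPI participants, give follow-up PHQ-9 and pain answers to, or with help from, the person who treated them. This is an avoidable, arm-asymmetric influence of unknown size and direction. The conclusion rests on the absence of any stated separation of duties, not on evidence that one person will do both. It does not show that the results would be biased, and correcting it would not remove the bias that comes with unblinded self-report. It is a cheap improvement.

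**What to change.** Replace the sentence that waives assessor blinding with a rule along these lines:

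- Post-intervention and 3-month questionnaires are completed by the participant alone by default.
- Collection, and any staff help, is done by a research assistant who did not deliver control calls and, where feasible with existing staff, is not told the allocation. That person reads items verbatim.
- Each form records whether help was given and by whom (nobody, caregiver, research assistant). This is reported by arm, descriptively.

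A re-analysis limited to unassisted forms should not serve as an inferential check. Help at follow-up arises after randomization and probably tracks impairment, so that subset would be small and selected.

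The cost is some scheduling effort, one extra item on each form and occasional accidental unmasking. Keeping the control-call provider away from follow-up forms should be possible with the two or more research assistants implied by Data analysis. Keeping the collector fully unaware of allocation is harder: the research assistant also prompts attendance, and two research assistants handle focus-group recordings, which involve PPI participants only. If full masking would need another person, the separation of duties is still worth making. The change should be in place before follow-up collection starts, because who helped cannot be reliably reconstructed later.
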